## Background

Bronchopulmonary dysplasia (BPD) is a common chronic lung disease whose incidence is increasing annually, especially in this time of the two-child policy in China [1, 2]. Patients with BPD usually have ventilator or oxygen dependence during the early stage of the disease [3]. Most patients can gradually withdraw from the ventilator or stop oxygen treatment at different times depending on disease severity, but abnormalities in pulmonary structure and lung function may last until late childhood and even adulthood, especially in those who are diagnosed as severe BPD according to the diagnostic criteria of the National Institute of Child Health and Human Development (NICHD) [4, 5]. The mortality of overall BPD patients is about 15% [6]; nevertheless, the mortality rate of severe BPD reaches 41%, creating an enormous threat to the health of these children [4, 7]. More than 50% of survivors with BPD experience hospital readmission for repeated lower respiratory infections in the first year or two, which causes serious economic and labor burdens on families [4, 8]. Although surfactant treatment [9], prenatal steroid usage [1, 10], ventilator strategies [11], and improved nutrition [12] are used in BPD patients, effective therapies are lacking [13]. Therefore, identifying novel effective therapies for severe BPD in children is urgent and significant.

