### Recruitment

Patients can only be enrolled in this study after passing the citywide consultation resolution and signing the informed consent form.

Participants will be recruited from three sources. First, the parents of potentially eligible hospitalized patients diagnosed with severe BPD will be approached and asked to join this study. Second, physicians will generate lists of patients from the electronic medical records of CHCMU with a diagnosis of BPD who were discharged within 1 year. Investigators or physicians will contact the patients’ parents by telephone or mail them a research leaflet and recruitment letter. Third, physicians will post study flyers at the outpatient department, the official website, and the WeChat public platform of CHCMU for those diagnosed with severe BPD at other hospitals. If the parents of these patients with severe BPD are interested in this research, we will initiate the screening process.

A multidisciplinary consultation will be held to confirm whether these potential participants meet the general diagnostic criteria of BPD as well as the inclusion and exclusion criteria. The consultation will consist of a neonatologist, a respiratory physician, a radiologist, a laboratory physician, a Department of Critical Care Medicine expert, stem-cell treatment center researchers, and medical department staff. If more than 80% of experts agree on the hUC-MSCs treatment, these patients will be viewed as potential participants. The researcher will then arrange a meeting to communicate with the legal representative or parents about the clinical trial research details and sign the written informed consent form.

The following details of the clinical trial will be fully explained to the patients’ guardians as follows: (1) study purpose; (2) research background; (3) number of participants and duration of their participation; (4) study procedures; (5) potential discomfort and risks of treatment; (6) expected benefits; (7) protection of confidentiality and privacy; and (8) their participation is voluntary. Each patient’s legal representative or parents will sign the informed consent form after all the items above are fully understood. After that, the patients’ baseline characteristics will be recorded by the clinicians (Table 2).

**Table 2 Tab2:** Timeline and items of evaluation during the trial

Items		Study period									
		Screening phase	Treatment phase				Follow-up phase				

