### Withdrawal

Discontinuation may occur due to participant death, severe adverse effects (SAEs), other serious disease-limiting participation, or study withdrawal requested by the guardian. If the participant withdraws from the trial, the reason for the withdrawal and all the results of observations will recorded in detail. Meanwhile, a new participant will be enrolled in the trial to replace the withdrawn subject.

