### Adverse events

AEs are defined as adverse medical events that occur after the subjects or their guardians provide written informed consent until the end of the study visit. AEs include abnormal laboratory results, symptoms, or diseases. All AEs will be recorded on a Case Report Form (CRF) and the researcher should provide comprehensive clinical reports. Once AEs occur, we will follow the principle of “the first priority of the participants,” take the necessary treatment according to the patients’ specific situation, and decide whether to suspend the clinical research. The main investigator should immediately inform the Scientific Research Office, Medical Service, and Ethics Committee of CHCMU. The SAE report should be submitted in writing within 24 h, while a follow-up SAE report should be submitted to the Human Research Ethics Committee.

An insurance policy will be prepared for all participants, who will be provided with ancillary and post-trial care in the case of injury or death as a result of their participation in the trial.

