### Outcome evaluation

The outcome measures and their time frames of this trial are listed in Table 3. The primary endpoint is the cumulative duration of oxygen therapy, i.e., the duration from starting to stopping oxygen treatment.

**Table 3 Tab3:** Outcome measures

Measures			Time frames
Primary outcomes	Cumulative duration of oxygen therapy		Until the time of stopping oxygen therapy
Secondary outcomes	Adverse events	Number of serious adverse events	Within 24 h post hUC-MSCs infusion
		Acute infusion associated adverse events	From the start of the trials to 1 month post hUC-MSCs infusion
		Late infusion associated adverse events	Within 2 years post hUC-MSCs infusion
	The rate of supplemental oxygen therapy		At 1 month post hUC-MSCs infusion
	Duration of invasive mechanical ventilation		
	Duration of noninvasive mechanical ventilation		
	The first time of stopping oxygen supplement		
	The rate of re-oxygen supplement		
	Pulmonary function changes		At 6, 12, and 24 months post hUC-MSCs infusion
	Chest radiography changes		
	Blood oxygen saturation		At 1, 3, 6, 12, and 24 months post hUC-MSCs infusion
	Mortality		
	Times of hospital readmissions		
	Complications of preterm birth		

The secondary endpoints include the safety and efficacy outcomes. The safety of the study will be assessed by the number of AEs including SAEs, acute infusion-associated AEs (AIA-AEs) and late infusion-associated AEs (LIA-AEs). SAEs include death, any malignant cardiac event (new ventricular tachycardia, ventricular fibrillation, or asystole, cardiac arrest), acute pulmonary embolism, stroke, anaphylactic shock, acute transplant rejection, and any other diseases extending the hospital stay. AIA-AEs include fever, general allergic reaction (rash, edema, erythema, pallor), infection at the injection site, vital sign changes, laboratory test changes (indicators of liver and kidney function, cardiac markers, indicators of hematology and immunity, markers of hepatitis/syphilis/HIV/tuberculosis, and urinalysis). LIA-AEs include tumorigenic events (tumor formation) and teratogenic events.

The efficacy endpoints are as follows: duration of oxygen therapy, duration of invasive mechanical ventilation, duration of noninvasive mechanical ventilation, the first time stopping the supplemental oxygen, rate of re-oxygen supplement, blood oxygen saturation, chest radiography changes, pulmonary function changes, mortality, number of hospital readmissions, and preterm birth complications.

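### Outside a short list of named events, the SAE definition covers other illness only if it extends a hospital stay, so a new admission of a discharged child is not clearly an SAE

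*Protocol article*

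**What the plan says.** The definition is in the protocol article, Outcome evaluation. It begins with named events: "SAEs include death, any malignant cardiac event (new ventricular tachycardia, ventricular fibrillation, or asystole, cardiac arrest), acute pulmonary embolism, stroke, anaphylactic shock". It ends with "acute transplant rejection, and any other diseases extending the hospital stay".

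Other sections bear on how it works:

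- **Recruitment.** Besides inpatients, candidates are sought in the hospital's records among children "with a diagnosis of BPD who were discharged within 1 year", and through flyers and online notices.
- **Follow-up procedures.** Contacts are by telephone at 1 and 3 months and at the outpatient clinic at 6, 12 and 24 months.
- **Background.** "More than 50% of survivors with BPD experience hospital readmission for repeated lower respiratory infections in the first year or two".
- **Adverse events.** All adverse events, diseases included, go on the CRF. For SAEs there is an added duty: "The SAE report should be submitted in writing within 24 h".
- **Table 3.** The number of serious adverse events is counted within 24 hours of infusion. Hospital readmissions are a separate secondary outcome, which the text places among the efficacy endpoints.
- **Safety monitoring.** The DSMB analyses all adverse events every 6 months.

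The abbreviation is expanded in different ways. The Withdrawal section has "severe adverse effects (SAEs"), the abbreviation list also uses *severe*, and Table 3 uses *serious*.

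**The concern.** The only general criterion presupposes that the child is already in hospital. For a child at home there is no stay to extend. Unless the illness is one of the named events, whether it counts as an SAE therefore depends on where the child was when it began and not on how grave it is.

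This matters here because the first study objective includes long-term safety, and because the Background presents readmission for lower respiratory infection as common among BPD survivors. SAE status also has consequences. It governs the 24-hour written report and its follow-up report, and it is one of the listed grounds for discontinuation, after which the child is replaced.

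The mixed use of *severe* and *serious* adds to the difficulty. Severity grades intensity and seriousness grades consequence, so the words alone do not tell staff which idea should decide a borderline case.

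**Working it through.** The protocol states no figure on this point, so there is none to reproduce. The check is to apply the wording to cases, and then to illustrate how often the gap could arise.

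**Step 1. Apply the definition as written.**

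- An inpatient has a mild infection and stays one day longer. The stay is extended: SAE.
- A child at home has a cardiac arrest, stroke, pulmonary embolism or anaphylactic shock, or dies. These are named events with no hospital condition: SAE.
- A child at home develops severe pneumonia at month 2, is admitted and survives. This is not a named event, and the illness starts a stay instead of extending one: not clearly an SAE.
- A child at home has life-threatening sepsis or respiratory failure and survives. The result is the same.
- An unnamed illness leaves lasting disability without extending a stay: not clearly an SAE.

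**Step 2. See whether another safety category takes these cases.** The acute infusion-associated category runs to 1 month and lists fever, allergic reaction, injection-site infection, and changes in vital signs and laboratory tests. The late category runs to 2 years and names only tumorigenic and teratogenic events. The month-2 pneumonia is not named in either. It remains an adverse event on the CRF and a readmission.

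**Step 3. See whether it would enter the SAE endpoint.** Table 3 stops that count 24 hours after infusion, so a month-2 event would stay out even under a wider definition. The 24-hour written report in the Adverse events section carries no such limit on when the event occurs. The definition therefore controls reporting, while definition and window together control the endpoint.

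**Step 4. Illustrate the frequency.** Inputs: 72 children, 24 per arm (Sample size and calculation); readmission of at least 50% of survivors (Background); mortality from the Background of 15% ("The mortality of overall BPD patients is about 15" per cent) and 41% ("the mortality rate of severe BPD reaches 41" per cent). It is an assumption that these apply to this trial.

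Children readmitted = 72 × (1 − mortality) × 0.50; the two infused arms are 48/72 of that if rates are equal across arms.

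| Mortality | Survivors | Readmitted | In the infused arms | Per arm |
|---|---|---|---|---|
| 41% | 42.5 | 21.2 | 14.2 | 7.1 |
| 15% | 61.2 | 30.6 | 20.4 | 10.2 |
| 0% | 72 | 36 | 24 | 12 |

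The two cited mortality figures give about 21 to 31 children, and no deaths would give 36.

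**The case against.** The strongest reply is that the events are not lost. Every adverse event goes on the CRF, Table 2 schedules adverse event evaluation at every visit from baseline to 24 months, readmissions are counted, and the DSMB reviews all adverse events every 6 months. This stands, and it confines the point to classification and expedited reporting.

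A second reply is that the list opens with *include*, so new admission is unlisted and not excluded, and that a journal article may leave detail to a fuller protocol. The first half is correct. But the article does not leave the definition open: it states one, with a general clause limited to extended stays. That clause gives staff no textual basis for reporting a new admission as an SAE.

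A reader might also infer more than the document supports:

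- *That no life-threatening illness in a discharged child is an SAE.* The named events count wherever the child is.
- *That the Ethics Committee would not hear of these events.* The Adverse events section can be read as requiring immediate notice to that committee of any adverse event. Only the 24-hour written SAE report and its follow-up are in doubt.
- *That readmissions escape causality review.* Nothing says so; the underlying illness is also an adverse event with its own clinical report.
- *That the protocol predicts 21 to 31 unreported cases.* The readmission rate is background literature on BPD survivors in general. Enrolled children may be up to 1 year old, so part of their risk period may precede entry, and several severe conditions are excluded.

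The inconsistent wording of the abbreviation is a minor matter in a single-centre trial with a list of named events, but it costs nothing to correct.

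**Conclusion.** The point holds in a limited form. The definition has one general criterion, extension of a hospital stay, in a trial that may enrol discharged children and follows them for 24 months largely through telephone and clinic contacts. A serious illness outside the named list that leads to a new admission, threatens life or causes lasting disability does not clearly meet it, and so does not clearly trigger the 24-hour written report. This is a stated rule that sorts events badly, not a detail left to another document.

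The demonstrated loss is in SAE classification and expedited written reporting. It is not shown that safety data go uncollected, nor that the definition alone would cause the SAE endpoint to understate harm, since the window in Table 3 would keep most later readmissions out anyway. The range of 21 to 31 children indicates how common the situation could be if the cited background rates applied; it is not an estimate for this trial. The change is worth making because it is cheap and improves safety reporting.

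**What to change.** 1. Replace the general clause in Outcome evaluation with: *any event that is fatal, life-threatening, requires or prolongs hospitalisation, or causes persistent disability*. Keep the named events as examples.
2. Use *serious* adverse event throughout: in the Withdrawal section, Outcome evaluation, Table 3 and the abbreviation list.
3. Link each admission recorded under the readmission outcome to an SAE form, so that both outcomes draw on one record.
4. If these events are meant to enter the SAE endpoint, change the 24-hour window in Table 3 as well. Either change alone leaves the other gap.

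The cost is wording in the protocol and CRF, and more SAE reports, because readmission is common in this population. Since SAEs are also a listed ground for discontinuation with replacement, the sponsor should check that the Withdrawal section still says what is intended once the term is wider. The sample size is unaffected.

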### Follow-up procedures

Follow-up assessments will be performed at 1, 3, 6, 12, and 24 months after the hUC-MSC injection (Table 2). The five follow-up points will be conducted by telephone and outpatient contact. The first two follow-ups will be performed at 1 and 3 months after the hUC-MSC treatment by telephone to ask the parents of the condition of their child(ren). The details of the telephone interview are shown in Table 4. The next three follow-ups will be performed at 6, 12, and 24 months at outpatient visits as shown in Table 5. The key outcome during follow-up will be changes on chest radiographs.

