**Methods:**

The MSC-BPD trial is a randomized, single-center, open-label, dose-escalation, phase-II trial designed to investigate the safety and efficacy of hUC-MSCs in children with severe BPD. In this study, 72 patients will be enrolled and randomly divided into two intervention groups and one control group. Patients in the intervention groups will receive a low dose of hUC-MSCs (*n* = 24; 2.5 million cells/kg) or a high dose of hUC-MSCs (*n* = 24; 5 million cells/kg) in combination with traditional supportive treatments for BPD. The patients in the control group (*n* = 24) will be treated with traditional supportive treatments alone without hUC-MSCs. The primary outcome measures will be cumulative duration of oxygen therapy. Follow-up assessments will be performed at 1, 3, 6, 12, and 24 months post intervention, and the key outcome during follow-up will be changes on chest radiography. Statistical analyses will evaluate the efficacy of the hUC-MSC treatment.

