		− 2 weeks	Baseline	24 hours	3 days	7 days	1 month	3 months	6 months	12 months	24 months
Therapy	hUC-MSCs	√	√								
	Traditional treatment	√	√	√	√	√					
Informed consent		√									
Inclusion and exclusion criteria		√	√								
Demographic information		√									
Personal history/past history/family history		√					√	√	√	√	√
Height/weight/head circumference		√	√			√	√	√	√	√	√
Vital signs^a^/physical examination		√	√	√	√	√			√	√	√
Hematology^b^/blood biochemistry^c^/urinalysis^e^		√	√	√							
Infectious disease-related examination^d^		√	√	√							
Blood oxygen saturation/blood gas analysis			√	√	√	√			√	√	√
Chromosome examination		√									
Brain MRI examination		√							√	√	√
EKG		√	√	√							
Echocardiogram		√									
Ventilator parameters/oxygen therapy			√	√	√	√	√	√	√	√	√
Adverse events evaluation			√	√	√	√	√	√	√	√	√
Chest high resolution CT			√						√	√	√
Pulmonary function test			√						√	√	√
Mortality/complications of prematurity^f^							√	√	√	√	√

Legend: *CK-MB* creatine kinase-MB*, CT*, computed tomography *EKG* electrocardiogram, *hUS-MSCs* human umbilical-cord mesenchymal stem cells

^a^The indicators of vital signs include temperature, blood pressure, heart rate, respiratory rate, transcutaneous oxygen saturation

^b^The condition of hematology of participants will be estimated by hematological tests which contains white blood cell count, platelet count, red blood cell count, hemoglobin, the percentage of lymphocytes, the percentage of neutrophil and C-reactive protein (CRP)

^c^The items of blood biochemistry include liver function, renal function, cardiac markers, the indicators of immunity, and the detailed items of each test are listed as follow. Liver function tests: albumin, bilirubin, alkaline phosphatase, alanine aminotransferase, aspartate aminotransferase, prothrombin time, activated partial thromboplastin time. Renal function tests: creatinine, blood urea nitrogen, creatinine clearance, glomerular filtration rate. Cardiac markers: hypersensitive troponin I, CK-MB mass, myoglobin

^d^Infectious disease-related examination include markers of hepatitis/syphilis/HIV/tuberculosis

^e^The content of urinalysis includes pH, protein, specific gravity, glucose and ketone bodies, white blood cells, occult blood or red blood cells, nitrite, color, and turbidity

^f^Complications of prematurity include growth retardation or retardation, hearing abnormalities, retinopathy, pulmonary hypertension, left ventricular hypertrophy

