### Randomization and blinding

Participants will be randomized into three groups in a 1:1:1 ratio after collection of the baseline data. The allocation sequence will be generated and sent to the investigators by a statistician. Participants will not be blinded during the phase-II trial and the patients in the control group will not be given hUC-MSC treatment.

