### Statistical analysis

SPSS version 17 (SPSS Inc., Chicago, IL, USA) statistical analysis software will be used to analyze the data in the study. Significant differences will be considered at an α level of 0.05.

The data will be examined at group assignment to the intervention and control groups using the *χ*^2^ test, *t* test or analysis of variance (ANOVA). For the intervention and control groups, the indicators at baseline and at 1 day, 3 days, 7 days, 1 month, 3 months, 6 months, 12 months, and 24 months will be compared with repeated measures ANOVA. Comparison of these outcome indicators including duration of oxygen therapy, duration of mechanical ventilation, pulmonary function tests, and quantitative scores of chest radiography changes between the intervention and control groups will be conducted using the *t* test. Mortality and hospital readmission rates will be tested by the *χ*^2^ test, while 24-month mortality will be analyzed by Kaplan-Meier curves.

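### The blinding section provides no masking for whoever scores the chest images, although that score is the named key follow-up outcome of an open-label trial and can be read masked

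*Protocol article*

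**What the plan says.** All references are to the protocol article.

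- **Role of the outcome.** The abstract says that "the key outcome during follow-up will be changes on chest radiography", and Follow-up procedures repeats this: "The key outcome during follow-up will be changes on chest radiographs". Table 3 lists chest radiography changes among the secondary outcomes, at 6, 12 and 24 months. The primary outcome is cumulative duration of oxygen therapy. Improvement in lung structure is part of the second study objective.
- **Form and analysis.** Under Statistical analysis, comparison of "quantitative scores of chest radiography changes between the intervention and control groups will be conducted using the *t* test". The scoring method is not described.
- **Imaging scheduled.** Table 2 lists "Chest high resolution CT" at baseline and at 6, 12 and 24 months.
- **Masking.** The abstract and the Discussion call the trial open-label. Randomization and blinding says: "Participants will not be blinded during the phase-II trial and the patients in the control group will not be given hUC-MSC treatment". It also has the statistician send the allocation sequence to the investigators. No section says whether the image scorer is masked.
- **Stated limitation.** The Discussion says that the trial falls short of a high-quality randomized design because it is open-label. It does not mention masked outcome assessment as a way to limit the consequences.

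**The concern.** A score assigned to an image can be influenced by what the scorer expects, and an expectation tied to the arm acts as a systematic difference between arms. A t test cannot separate such a difference from a treatment effect.

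The primary outcome depends on bedside decisions to stop oxygen, which are hard to shield when families and clinicians know the treatment. A stored scan is different: it can be scored later by someone who does not know the arm. It is therefore one of the easiest outcomes in this trial to protect, and it is the one the article calls key for follow-up. If it too is read with the arm known, the trial's evidence on lung structure is exposed to the same open-label bias as its bedside outcomes.

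**Working it through.** **1. Does any text mask the scorer?** The section headed Randomization and blinding covers participants and stops there. The trial is run at one hospital, and the allocation sequence goes to the investigators. Follow-up procedures, Data collection and Statistical analysis say nothing about who scores the images or what that person knows. A trial run as described would let the scorer know the arm, but the article does not say that this will happen.

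**2. Does open-label treatment explain the gap?** No. Open-label describes knowledge of treatment among families and clinicians. The scans are stored images, scheduled at fixed visits, and can be de-identified before scoring. The Discussion's reasoning, that open-label status rules out a high-quality design, does not extend to this outcome.

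**3. The plan's own figure.** The only sample size given is for the primary outcome (Sample size and calculation: SD 15 days, differences of 13 and 18 days, alpha 0.05, power 0.80). With n per group = 2 (1.960 + 0.842)² SD² / difference²:
- low dose: 2 × 7.85 × 225 / 169 = 20.9, so 21
- high dose: 2 × 7.85 × 225 / 324 = 10.9, so 11

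The larger is 21, and 21 / 0.90 = 23.3, so 24 per group. The stated 21 and 24 are reproduced. No corresponding figure exists for the imaging score, and masked reading changes none of these numbers.

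**4. Illustration of what a reading shift would do.** The documents give no SD for the score and no estimate of reader bias, so the shift b is assumed and expressed in SDs of the score. The true effect is set to zero. The test is a two-sample t test of one dose arm against control at one time point, at alpha 0.05. It is taken as two-sided, because the article does not state sidedness.

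- Degrees of freedom = 2n − 2; noncentrality = b × √(n/2).
- False-positive rate = P(T > t) + P(T < −t), with T noncentral t and t the 97.5% point of the central t.
- n = 24: 46 degrees of freedom, √12 = 3.464.
- n = 21: 40 degrees of freedom, √10.5 = 3.240.

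| Assumed shift (SD) | Noncentrality, n = 24 | Rate, n = 24 | Rate, n = 21 |
|---|---|---|---|
| 0 | 0 | 5.0% | 5.0% |
| 0.1 | 0.346 | 6.3% | 6.2% |
| 0.2 | 0.693 | 10.4% | 9.7% |
| 0.3 | 1.039 | 17.4% | 15.8% |
| 0.5 | 1.732 | 39.6% | 35.3% |

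The n = 21 column shows the number per arm left after the loss the plan allows for. Nearly all the excess lies in the direction of the shift: at 0.2 SD and n = 24, 10.0 of the 10.4 percentage points do.

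**The case against.** The strongest objection is that this rests on silence. The article condenses a fuller protocol that is not shown, and reading procedures may sit there or in an imaging manual. The outpatient follow-up list (Table 5), the flow diagram and the SPIRIT file are not shown either. A reader might infer that the scans will be read by someone who knows the arm. The documents do not say so, and that inference should not be reported as fact. The point still stands as a design gap, because the article has a section on blinding, that section stops at participants, and the Discussion presents open-label status as a limit on quality with no mitigation for its own key follow-up outcome.

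Other limits on the point:

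- **Importance.** A reader might take the imaging score as the basis of the trial's main efficacy claim. Table 3 makes it secondary, and the only powered outcome is oxygen duration.
- **The eligibility panel.** The section on recruitment says: "The consultation will consist of a neonatologist, a respiratory physician, a radiologist". A reader might see this as a source of bias. It is not evidence of any: the panel sits before randomization, when there is no arm to know, and nothing says that this radiologist scores follow-up scans.
- **Subjectivity.** The article says the scores are quantitative but not whether they are visual or computed by software. A largely automated score would leave less room for expectation.
- **Size.** No document supports any particular shift, or its direction. The arithmetic is correct, but it illustrates sensitivity and does not estimate bias.
- **Masking the visit.** Children enrolled in the first year of life and scanned up to 24 months later will differ visibly in size, so this is largely impractical. A between-arm comparison needs only the arm masked.

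**Conclusion.** The point holds in this form: an open-label trial names a quantitative chest-imaging score as its key follow-up outcome and compares it between arms, and its blinding section provides no masking for whoever scores the images. Knowledge of the arm can bias that comparison. Whether it would, and by how much, cannot be known from the documents.

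Under the stated assumptions (24 per arm, no true effect, two-sided test, shift of 0.2 to 0.3 SD), the false-positive rate of one comparison would be about 10% to 17% in place of 5%. The sample size and the primary analysis are unaffected. The correction is worth making because the outcome is one the article itself singles out, and the protection is available despite open-label treatment.

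**What to change.** State in Randomization and blinding, and again in Follow-up procedures, that:

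- the baseline, 6-, 12- and 24-month chest scans already in Table 2 are de-identified and scored in random order by whoever already scores them, masked to allocation;
- only these masked scores enter the between-arm comparison described under Statistical analysis.

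Masking of the visit is not required. If masked reading is already planned in a document not shown, one sentence in the blinding section settles the matter.

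The cost is modest work to de-identify and batch the images, and study scores that become available later than clinical readings. No extra scan or participant is needed and, if the person who already scores the scans does it, no extra reader.
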